## Abstract

**Background:**

As treatment of choice in promoting psychological flexibility, Acceptance and Commitment Therapy (ACT) was found to be effective in several conditions, and among different populations, including weight management in individuals with obesity. However, the mechanism of action of psychological flexibility is less known. The aim of the present study is, within the context of a brief ACT intervention for behavioral change and behavioral maintenance of a healthy lifestyle in a sample of inpatients with obesity, to explore the effect of each subcomponent of the psychological flexibility model on treatment processes and outcomes.

**Methods:**

A randomized controlled trial will be conducted. Ninety Italian adult inpatients with obesity attending a rehabilitation program for weight loss will be randomly allocated into three experimental conditions targeting respectively each subcomponent of the psychological flexibility model: group Engage focused on values-oriented behaviors, group Openness focused on acceptance and cognitive defusion, and group Awareness focused on being present and aware of thoughts, feelings, and behaviors at every moment. Weight, BMI (kg/m^2^), the Psychological General Well-Being Inventory (PGWBI), the Outcome Questionnaire-45.2 (OQ-45.2), the Depression Anxiety and Stress Scale (DASS-21), the Difficulties in Emotion Regulation Scale (DERS), the Dutch Eating Behaviors Questionnaire (DEBQ), the Brief Values Inventory (BVI), the Committed Action Questionnaire (CAQ), the Italian-Cognitive Fusion Questionnaire (I-CFQ), the Five Facet Mindfulness Questionnaire (FFMQ), and the Acceptance and Action Questionnaire (AAQ-II) will be assessed at the beginning (time 0), at the end of psychological intervention (time 1), and after 3 (time 2) and 6 months (time 3) and 9 months (time 4) from discharge. During the following month after discharge, outpatients will be monitored in their adherence to a healthy lifestyle, using a wearable device.

To assess the effectiveness of the intervention, mixed between-within 3 (conditions) × 4 (times) repeated measure ANOVAs will be conducted to examine changes from time 0 to time 1, 2, 3, and 4 in means of weight, BMI, and means of scores PGWBI, OQ-45.2, DASS, DERS, DEBQ, AAQ-II, BVI, CAQ, I-CFQ, and FFMQ, between three groups.

**Discussion:**

This study will contribute to clarify the mechanism of action of each subcomponent of the psychological flexibility model and understand its impact on the promotion of a healthy lifestyle.

**Trial registration:**

ClinicalTrials.govNCT04474509. Registered on July 4, 2020

## Background

Obesity is one of the most serious health problems in global public health [1]. Recent estimates pointed out that over the last years obesity reached epidemic proportions, and its prevalence is still rising. In 2016, over 1.9 billion adults in the world were overweight and, of these, more than 650 million were obese [2].

Defined as an excess of body weight, obesity is a significant risk factor for a plethora of physical, psychological, and social problems, all of which can heavily impact health, quality of life, and global functioning. Obesity is frequently associated with many physical comorbidities, including type II diabetes mellitus, cardiovascular disease, hypertension, kidney failure, and osteoarthritis [3]; psychological problems such as depression, feelings of shame, low self-esteem, and stigma [4]; and eating disorders, as well as social and economic impairment [5].

Given the complex nature of the phenomenon, comprehensive multidisciplinary and multi-component lifestyle interventions for the management of obesity in adults are recommended. They include nutrition and dieting, physical activity, and psychological support, aimed at fostering the adoption of a healthy lifestyle through the Cognitive Behavioral Therapy-based interventions considered the gold standard for the treatment of obesity [6].

Even if such programs have been recognized as effective in promoting healthy lifestyle adoption, the maintenance of behavioral change remains challenging. Most obese or overweight people who attend a weight loss rehabilitation program fail to maintain a healthy lifestyle over time. As a consequence, they regain about one-third of the weight lost over the following year after treatment [7, 8]. This evidence has spurred research to investigate which factors represent barriers to weight loss maintenance and which factors may influence the adoption of healthy lifestyle habits.

Forman and Butryn’s conceptual model [9] suggest that long-standing adherence to a healthy lifestyle is partially due to some self-regulation skills, such as distress tolerance, values clarity, metacognitive awareness, and behavioral commitment. Such skills were found to play a protective role against the excessive responsiveness to such internal (such as emotions) and external (the availability of tasty food in the modern environment) cues that motivate people to eat palatable food in response to negative internal states, as in case of emotional eating.

Emotional eating refers to eating in response to unpleasant emotional states [10]. Since emotional eating has been associated with elevated consumption of high-calorie and high fat, it does not surprise that emotional eating was found to be strongly related to obesity [11] both in adults and in the younger population [12, 13].

The link between negative emotions and emotional eating has been well-established both in general [14] and in obese population [15]. Many studies suggested that dysfunctional eating habits, such as emotional eating, may emerge as a failure of emotion regulation strategies that allow individuals to regulate their own emotions by modulating their responses [16, 17]. As a result, individuals eat in an attempt to regulate their negative internal states.

The treatment of choice to promote self-regulation skills is Acceptance and Commitment Therapy (ACT [18];). ACT is one of the recent third-wave Cognitive Behavioral Therapies (CBTs) rose in the last 20 years. It is a transdiagnostic approach aimed at promoting psychological flexibility defined as the ability of “being in contact with the present moment fully as a conscious human being and, basing on what the situation affords, changing or persisting in behavior in the service of chosen values” [18]. The promotion of psychological flexibility is based on three subcomponents of the psychological flexibility model: openness, awareness, and engagement. Openness refers to the willingness to develop an open and acceptable attitude toward one’s personal internal states such as thoughts, emotions, and bodily sensations; awareness refers to the ability to act intentionally with awareness about personal thought and sensations, without automatically reacting; engagement refers to engage oneself in committed behaviors related to personal values, that is chosen life directions [19].

Over the years, ACT has been successfully applied in various pathological conditions, including obesity management both in adult and young populations [20–22]. In an RCT [23] comparing a standard CBT-based group psychological intervention with an ACT-based group psychological intervention within an in-hospital multidisciplinary rehabilitation program for weight loss for patients with obesity, it was found that, since there were no significant differences between groups from pre- to post-interventions in weight reduction (both groups showed a decrease of weight and BMI from pre- to post-intervention), only participants in the ACT condition were able to maintain weight lost during the intervention, over the following 6 months after discharge. About the psychological conditions, CBT was greater than ACT in producing improvement in the psychological conditions (subjective well-being, psychological problems, life functioning, risk for self-harm or harm others) from pre- to post-intervention. On the contrary, at 6-month follow-up, the effect of the intervention was more extensive in the ACT condition than in CBT. The difference between the two interventions was reasonably attributed to the intrinsic different goals of the therapy: while CBT is focused on the reduction of symptoms [24], providing an immediate—but not lasting—relief, ACT fosters psychological flexibility, considered the core mechanism of action of therapy [18].

In the field of health promotion, it was found that psychological flexibility fosters the adoption and the maintenance of behaviors which are driven by personal values and promotes an open, willing, and accepting attitude toward internal and external undesirable private events such as thoughts, emotions, and bodily sensations. Finally, it improves the ability to be present in the moment and face events in the context they happen [25].

Even if it has been well-established that psychological flexibility is the core mechanism of action in the ACT-based interventions, less is known about how each subcomponent acts.

To the authors’ knowledge, only one study [26] has previously explored the specific effect of two subcomponents of the ACT on treatment processes and outcomes in 15 adults seeking mental health treatment, founding that both the modules—one targeting acceptance and defusion, and one targeting values-based activation—produced improvements in psychiatric symptoms and quality of life, as well as improvements in specific therapeutic processes. However, no study has already assessed the specific effect of every single subcomponent of the psychological flexibility model, in weight management.

On the basis of these premises, the aim of the current study is to assess—within the context of a brief ACT-based intervention aimed to promote the adoption and maintenance of healthy lifestyle behaviors in a sample of Italian adult individuals with obesity—the specific effect of each subcomponent of the ACT model on the promotion and, most importantly, the maintenance of a healthy lifestyle.

The intervention will be part of a multidisciplinary 1-month rehabilitation program for weight loss.

## Methods

### Study design

An equivalent randomized controlled trial (RCT) with parallel groups will be conducted. We will perform a simple randomization with 1:1:1 allocation ratio using a computer-generated randomization (www.randomization.com). Allocation concealment will be ensured since all the patients will generate an anonymous code that will be associated to the randomization’s sequence generated by the program. Researchers will be blinded to the association made.

Since we already assessed the efficacy of an ACT-based intervention compared to a CBT-based intervention in the same context of obesity rehabilitation in a previous study [23], in this study, the aim was to compare the three subcomponents of the psychological flexibility model with each other.

Thus, participant enrolled for the study will be randomly allocated into three experimental conditions, targeting respectively each specific subcomponent of the psychological flexibility model:
Group *Engage*Group *Openness*Group *Awareness*

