### Participants

Ninety Italian adult individuals with obesity (BMI ≥ 30) attending a multidisciplinary rehabilitation program for weight loss in a single clinical center in the North of Italy will be recruited for the study if they met the following criteria assessing in a clinical interview: (1) age between 18 and 65 years, (2) BMI ≥ 30, (3) being technology friendly to use wearable devices, and (4) written and informed consent to participate.

Exclusion criteria for the study are (1) any psychiatric disturbances (including eating disorders, diagnosed according to DSM 5 criteria) and (2) any medical conditions that could compromise participation at the study.

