### Statistical analysis

Data will be analyzed basing on intention-to-treat. This analysis includes all randomized patients in the groups to which they are randomly assigned, regardless of their adherence with the entry criteria, regardless of the treatment they actually received, and regardless of subsequent withdrawal from treatment or deviation from the protocol. Incidence, mechanisms, and patterns of missing data will be explored. To assess if missing data follow a Missing Completely At Random, Little’s MCAR test will be employed. Missing data lower than 5% will be considered negligible. In case of further amount of missing data, multiple imputation will be used.

Sample size has been calculated for a 3 (between) × 4 (within) ANOVA using G*Power software (release 3.1.3) [50]. Setting alpha to 0.05, power to 0.80, and possible dropout, a total sample of 90 is considered enough to detect a small effect size (*f* = 0.20).

Descriptive statistics (such as means, standard deviations, skewness, and kurtosis) will be conducted to explore the characteristics of the sample and assess for the normal distribution of the variables. Differences between baseline characteristics of the sample will be explored using one-way analysis of variance (ANOVA). To assess relations between variables, correlational analysis will be performed. Chi-squared for categorial variables and Pearson’s correlations for continuous variables will be used. To assess the effectiveness of the intervention, mixed between-within 3 (conditions) × 4 (times) repeated measure ANOVAs will be conducted to examine changes from time 0 to time 1, 2, 3, and 4 in means of weight, BMI, and means of scores PGWBI, OQ-45.2, DASS, DERS, DEBQ, AAQ-II, BVI, CAQ, I-CFQ, and FFMQ, between three groups. Corrected effect sizes (Hedges’s *g*) and significance at 95% confidence interval (95% CI) will be calculated for both between-group and within-group differences.

In order to assess adherence to healthy lifestyle recommendations, total means of each daily registered indicator of a healthy lifestyle will be calculated, as well as differences of the same parameters between groups, using one-way ANOVAs.

Analysis will be performed using IBM Statistical Package for the Social Sciences (SPSS) version 26.

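### Simple randomisation of 90 patients is valid, but the wearable outcomes have no baseline and an unadjusted test, so a chance imbalance in sex or BMI would go uncorrected

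*Protocol article*

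**What the plan says.** **Allocation (Study design).** "We will perform a simple randomization with 1:1:1 allocation ratio using a computer-generated randomization". Patients are "randomly allocated into three experimental conditions, targeting respectively each specific subcomponent of the psychological flexibility model". The section names no blocks, strata or minimisation.

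**Population (Participants).** "Ninety Italian adult individuals with obesity (BMI ≥ 30) attending a multidisciplinary rehabilitation program for weight loss in a single clinical center". Eligibility is "1) age between 18 and 65 years, (2) BMI ≥ 30", with no upper BMI limit stated.

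**Outcomes (Measures, Lifestyle, Procedures).** Adherence to a healthy lifestyle is listed among the primary outcomes, although the Lifestyle subsection is printed under the secondary-outcomes heading. It is recorded as activity minutes, total calories and steps. Gender, weight and height are collected at time 0. The wearable devices are handed out only at discharge and used for one month.

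**Analysis (Statistical analysis).** Weight, BMI and the questionnaires are analysed by group-by-time repeated-measures ANOVA as changes from time 0. For the lifestyle indicators the plan takes the mean of each daily indicator, "as well as differences of the same parameters between groups, using one-way ANOVAs". No covariate is named. Baseline characteristics are compared by one-way ANOVA, and nothing is said to follow from the result.

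**Sample size (Statistical analysis).** The basis is given as "Sample size has been calculated for a 3 (between) × 4 (within) ANOVA using G*Power software". On the inputs, the section says: "Setting alpha to 0.05, power to 0.80, and possible dropout, a total sample of 90 is considered enough". The target is an f of 0.20, which the article calls small.

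**The concern.** Three features coincide for the wearable indicators: allocation that does not balance patient mix, no pre-treatment value of the outcome, and a test with no covariates. For these outcomes, nothing in the stated design or analysis offsets a chance difference between arms in who the patients are.

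The trial compares three variants of one brief therapy with each other, without an untreated arm, and maintenance of a healthy lifestyle is what the stated aim stresses most. If sex and BMI predict steps, activity or calories, a chance difference in patient mix could be read as an effect of one ACT component, or could hide one. The article itself sets the recommended calorie intake relative to each patient's estimated basal energy expenditure, yet compares raw means between arms.

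**Working it through.** **1. The plan's own figure.** Inputs from the article: k = 3 groups, m = 4 times, f = 0.20, alpha = 0.05, N = 90. For the group-by-time interaction, lambda = f²·N·m/(1 − rho), with (k − 1)(m − 1) = 6 and (N − k)(m − 1) = 261 degrees of freedom.
- rho = 0: lambda = 0.04 × 90 × 4 = 14.4 and power is 0.814. The smallest N for 80% power is 88.
- rho = 0.5: lambda = 28.8 and power is 0.99. The smallest N is 45.
- Between-group main effect at rho = 0.5: power 0.55 at 90; N = 156 is needed.

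The article gives no rho, no tested effect and no dropout rate, so 90 cannot be reproduced uniquely. The present point does not depend on it. None of these calculations covers the wearable comparison, which has one mean per patient. There lambda = f²·N = 0.04 × 90 = 3.6 on 2 and 87 degrees of freedom, and power at f = 0.20 is 0.37. Precision is therefore scarce for these outcomes.

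**2. How often arms differ by chance.** Simulation of 90 patients and three arms (20,000 to 200,000 draws). Assumptions: 30% to 50% men, and standardised normal BMI. The gap is the largest difference between any two arms. The stratified scheme uses blocks of 6 within sex by BMI (median split).

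| Event | Simple | Fixed 30/30/30 | Stratified blocks |
|---|---|---|---|
| Sex gap ≥ 20 points | 22–28% | 26–33% | 0% |
| BMI gap ≥ 0.5 SD | 13–14% | 13% | 0.6% |
| Either of these | 32–38% | 36–41% | 0.6% |
| BMI gap ≥ 0.25 SD | 60% | 60% | 27% |

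Under simple randomisation the largest and smallest arms differ by about 9 patients on average, and by 10 or more in about 43% of trials. Equal arm sizes alone do not reduce covariate imbalance.

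**3. What an imbalance does to an unadjusted one-way ANOVA.** Type I error, with r the assumed correlation between BMI and the outcome:

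| r | All trials, unadjusted | BMI gap ≥ 0.5 SD, unadjusted (two runs) | BMI gap ≥ 0.5 SD, ANCOVA |
|---|---|---|---|
| 0.3 | about 5% | 6.5%, 7.5% | 4.6% |
| 0.5 | about 5% | 11.6%, 11.2% | 4.2% |
| 0.7 | about 5% | 19.8%, 19.3% | 3.9% |

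The ANCOVA column rests on about 1,650 imbalanced trials per row, so its simulation error is about √(0.05 × 0.95/1650) = 0.5 points. The values are at or near the nominal 5%. At r = 0.5, the trials without such a gap have an error of (0.0508 − 0.1345 × 0.112)/(1 − 0.1345) = 4.1%. The overall 5% thus averages a slightly low error in most trials with a raised one in a few.

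**4. Size of one shift.** If the sexes differ by 0.5 to 1.0 SD on an outcome (assumption), a 20-point sex gap shifts an arm difference by 0.20 × 0.5 = 0.10 to 0.20 × 1.0 = 0.20 SD. The standard error of a difference with 30 per arm is √(2/30) = 0.26 SD, so the shift is 0.4 to 0.8 of a standard error.

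**5. Precision gained by adjustment.** Adjustment multiplies the residual variance by 1 − r². For r = 0.3, 0.5 and 0.7 that is 0.91, 0.75 and 0.51. Before the small loss for two extra coefficients, 90 patients then count as 90/0.91 = 99, 90/0.75 = 120 and 90/0.51 = 176.

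**The case against.** Much of the case on the other side stands.

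- **Simple randomisation is not an error.** It is unbiased, the unadjusted ANOVA keeps about 5% type I error overall, and it is the least predictable scheme. A reader might infer that the allocation method biases the trial. Nothing in the article supports that.
- **Weight and BMI are not exposed in the same way.** A reader might extend the worry to them. They have time 0 values and are analysed as change, so a baseline difference in level largely drops out of the group-by-time contrast. The same holds for the questionnaires.
- **The imbalance is usually modest.** More than 70% of trials escape a 20-point sex gap, about 86% escape a 0.5 SD BMI gap, and the shift in step 4 is below one standard error. Unequal arms matter little: 24 against 33 patients gives √(1/24 + 1/33) = 0.268, about 4% above 0.258.
- **The strength of the predictors is assumed.** The article does not say that sex or BMI drives steps or activity. Only its calorie recommendation is scaled to the individual.
- **The planned f gives no safe benchmark.** Converting f = 0.20 to 0.20 × √6 = 0.49 SD between extreme arms treats a repeated-measures f as a between-group f, which the article does not establish. No conclusion here rests on it.
- **An imbalance would be visible and adjustable, and covariates are often left to the analysis plan.** This is true, and it is why the remedy is cheap. But the article does name the test for the wearable indicators, and that test takes no covariates. It attaches no consequence to the baseline comparison.

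**Conclusion.** The point holds for the wearable indicators only. With no baseline and a test without covariates, those comparisons give up precision and have no protection against an unlucky draw. Under the stated assumptions, about one trial in three (32% to 38%) has a sex gap of at least 20 points or a BMI gap of at least 0.5 SD. In the 13% to 14% with the BMI gap, type I error rises to roughly 7%, 11% or 19% for correlations of 0.3, 0.5 or 0.7. If sex and BMI barely predict the indicators, little is lost either way. The consequence is lost precision and error conditional on imbalance, not bias. This is an improvement to make, not a flaw that invalidates the trial.

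**What to change.** **Free improvement.** In Statistical analysis, replace the one-way ANOVAs of the lifestyle indicators with ANCOVAs that include sex and time 0 BMI (continuous). Prespecify these covariates whatever the baseline tests show. Both variables are already collected, so the cost is two model terms and two degrees of freedom. The Trial status section dates data collection from March 2021, so allocation may have started. This change is still possible if it is fixed before the arms are compared.

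**Cheap improvement, only if allocation has not begun.** In Study design, generate the list in permuted blocks of randomly varying size (for example 3 and 6), stratified by sex and BMI class, and keep those strata in the models. In the simulation (blocks of 6, median BMI split) this cut the chance of either large imbalance to 0.6%. It needs no extra patients or visits. The downside is that some allocations at a single centre become guessable. Random block sizes and keeping the list away from recruiters limit this.

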### Participants

Ninety Italian adult individuals with obesity (BMI ≥ 30) attending a multidisciplinary rehabilitation program for weight loss in a single clinical center in the North of Italy will be recruited for the study if they met the following criteria assessing in a clinical interview: (1) age between 18 and 65 years, (2) BMI ≥ 30, (3) being technology friendly to use wearable devices, and (4) written and informed consent to participate.

Exclusion criteria for the study are (1) any psychiatric disturbances (including eating disorders, diagnosed according to DSM 5 criteria) and (2) any medical conditions that could compromise participation at the study.

